# A Personalized, Home-Based, Multidisciplinary Outpatient Clinic for Managing Breathlessness in Chronic Obstructive Pulmonary Disease: Protocol for a Single-Arm, Mixed-Methods Cohort Study

**DOI:** 10.2196/85766

**Published:** 2026-04-02

**Keywords:** chronic obstructive pulmonary disease, COPD, breathlessness, multidisciplinary, chronic disease management, breathlessness intervention service

## Abstract

**Background:**

Breathlessness is a distressing symptom for people with chronic obstructive pulmonary disease (COPD), impacting independence and community participation, resulting in reduced quality of life. With optimized treatment, nonpharmaceutical interventions deployed in a home-based breathlessness intervention service may reduce breathlessness to a manageable level.

**Objective:**

The aim of this study is to investigate whether patients with COPD experience reduced burden of chronic breathlessness and health care use following participation in the Macarthur Breathless Clinic (MBC), a multidisciplinary home-based health service intervention and to explore participant and carer experiences.

**Methods:**

The proposed research is a single-site, mixed methods, single-arm cohort study evaluating MBC. Eligible participants will have chronic breathlessness as defined by a modified Medical Research Council score of at least 2 and COPD confirmed by spirometry. Initially, participants will undergo a holistic medical assessment to understand factors contributing to breathlessness and to optimize therapy. The MBC intervention will be a 9-week, home-based, multidisciplinary program (with contributions from medical, nursing, physiotherapy, and occupational therapy clinicians). Central to this program will be coaching for breathlessness self-management using individualized, multicomponent strategies. Breathlessness impact will be assessed using questionnaire instruments measuring breathlessness mastery, symptom burden, quality of life, and psychological distress, with the Chronic Respiratory Questionnaire’s mastery subscale as primary outcome. Assessments will be undertaken at baseline, 9 weeks, and 52 weeks; 12-month exacerbation rates, health care use, and rescue medication use will be monitored and measured against participants’ historical data. Participant and carer experiences will be evaluated using qualitative methods to inform development of the service.

**Results:**

This project was funded in stages according to defined milestones, with the final milestone payment received in October 2025. Data collection commenced in March 2022. On submission of this manuscript, recruitment is complete with 92 participants having completed the protocol by March 2024. Data analysis is ongoing, and results are expected to be reported by early 2027.

**Conclusions:**

This research protocol is the first to investigate long-term outcomes following a health service intervention targeting chronic breathlessness for patients with COPD. Positive results may see breathlessness strategies from MBC or other similar health service interventions incorporated into existing models of chronic COPD care.

**Trial Registration:**

Australian and New Zealand Clinical Trial Registry ACTRN12620001330932; https://tinyurl.com/35fec8h4

**International Registered Report Identifier (IRRID):**

DERR1-10.2196/85766

## Introduction

Chronic obstructive pulmonary disease (COPD) is a multisystem disease, primarily affecting the lungs and characterized by incompletely reversible airflow obstruction [1]. COPD is common, affecting 10% of adults worldwide and 14% of Australians aged >40 years [2]. Despite treatment according to guidelines, people with COPD experience a range of symptoms. Breathlessness is often prominent among these and may contribute to physical and psychological distress, and reduced functional status and community participation [1]. Breathlessness is responsible for a high proportion of ambulance presentations, medical admissions, and health care costs [3,4]. However, patients with refractory breathlessness and their caregivers feel that there is a lack of awareness of the symptom burden among health care providers and insufficient provision to address this burden within health care services [2,5,6].

Breathlessness intervention services have been clearly shown effective in reducing the burden of breathlessness for populations with malignant and mixed etiology disease [7]. Existing breathlessness intervention service research primarily targets participants with malignant disease, in Europe, over a 4- to 6-week period, led by clinicians whose expertise is in palliative care [7]. An Australian protocol for a single-blind, randomized, parallel-group study investigating the impact of a breathlessness intervention service on people with COPD has been published; however, the study outcomes are not yet fully reported [8].

The primary aim of this study is to assess whether participants living with COPD will experience reduced breathlessness impact following participation in a bespoke 9-week intervention, the Macarthur Breathless Clinic (MBC), focused on nonpharmacological interventions such as breathing retraining, energy conservation, physical activity, and use of a handheld electric fan. A secondary aim is to monitor participants’ exacerbations, health care use, and rescue medication use after the intervention for comparison with past patterns of disease activity. Furthermore, we will use qualitative methods to assess patient and caregiver experiences.

The hypothesis is that patients with COPD will experience (1) reduced impact of breathlessness (in terms of coping ability, symptom burden, quality of life, and psychological distress); (2) reduced COPD-related health care use; and (3) report a positive consumer experience following participation in the MBC.

## Methods

### Study Design

This research is a prospective, single-arm cohort study of MBC, a breathlessness intervention service, assessed using mixed methods. The intervention is designed to adapt to incorporate components found to work well and to discard or revise those found to be less effective, informed by the experience of conducting the program.

Quantitative outcomes will be evaluated with participants acting as their own controls, before and after the clinic intervention. A 12-month follow-up with sequential cross-sectional assessments will provide an opportunity to assess breathlessness impact, exacerbations, health care use, and durability of outcomes. Qualitative outcomes for patients and their carers, if applicable, will be sought via an interviewer-administered survey in the months following completion of the clinic intervention. A flow diagram overview of the study design is shown in Figure 1.

**Figure 1 figure1:**
[figure not shown]
Study design. Allocated percentages are estimates only. ECOPD: exacerbation of chronic obstructive pulmonary disease; HCU: health care use.

### Ethical Considerations

This study protocol has been approved by the South Western Sydney Local Health District’s Human Research Ethics Committee on December 1, 2020, and is listed on the Australian and New Zealand Clinical Trial Registry (ACTRN12620001330932). The research will be conducted in accordance with the principles of the World Medical Association Declaration of Helsinki, ensuring participant safety, data confidentiality, and adherence to all ethical guidelines. Written informed consent will be obtained from each participant after they have been fully advised of the study aims, methods, potential risk and benefits, their right to withdraw at any time without reprisal, and the measures to protect their privacy and confidentiality. Participation will be entirely voluntary, and no monetary compensation, gifts, or incentives will be provided to participants in exchange for their time or information.

### Setting

The study will be conducted predominantly within participants’ homes across the Campbelltown, Camden, and Wollondilly local government areas in Sydney, Australia. This is an area on the fringe of metropolitan Sydney that accommodates a population with ethnic and linguistic diversity, social disadvantage, and a comparatively high proportion of Aboriginal Australians. In addition to home visits, a maximum of 2 scheduled health care interactions will occur in selected outpatient sites within the Macarthur Health Service.

### Recruitment

Clinician referrals will be sought via outpatient services or after stabilization following hospital admission for COPD-related illness. Referrals will be screened by research personnel to ensure eligibility. Previous piloting of this mode of referral and recruitment has demonstrated feasibility for achieving the recruitment target over 12 months.

Where applicable and with patient agreement, carers will be invited to participate in the trial to contribute qualitative data to reflect on their support person role and perceptions of the service.

### Sample Size

Recruitment target estimation is constrained by limited precedent data, most of which originate from research undertaken in the United Kingdom, studying participant populations, interventions, and outcomes that differ to ours [7,8]. However, pilot data from Westmead Hospital’s Breathlessness Clinic for patients with COPD (similar target population to that proposed in this study) demonstrated statistically significant and clinically relevant outcome improvements in preliminary analysis of only 10 participants [9]. The currently proposed model has been informed by their prior experience. To allow for the substantial losses to follow-up commonly seen in clinical trials in moderate to severe patients with COPD, we have set our recruitment goal at 92 participants, in anticipation of 30% (n=31) discontinuation or dropout.

### Data Collection Methods

All participant clinical and demographic data, as well as baseline and subsequent outcome data, will be collected by nonclinician MBC staff to minimize social acceptance bias. To ensure consistency in data evaluation, the same staff members will, where possible, collect outcome data for individual patients throughout the study.

A combination of outcomes has been chosen to comprehensively assess the intervention. Breathlessness impact will be measured using standardized questionnaires. These questionnaires will be administered in a pen-and-paper format in the home setting by interviewers without detailed knowledge of the intervention to further reduce bias. Participants will attempt questionnaire responses uninformed about their previous results but can be prompted with this information, if needed, in the event that the participant is otherwise unable to respond.

Health care use and exacerbation data will be gathered through structured interviews with participants. These interviews will be designed to capture detailed information about health care visits, hospitalizations, and other relevant health care interactions over the study period. The self-reported data from these interviews will be systematically cross-referenced with participants’ health records to improve accuracy.

Qualitative data will be collected through in-depth interviews using a predefined semistructured interview script for both participants and carers. After obtaining permission, interviews will be recorded and transcribed verbatim for subsequent analysis. After transcription, recordings will be destroyed, and transcripts will be stored in the participant research files.

The purpose of surveying participant and carer experiences is partly a pragmatic attempt to inform development and adaptation of the clinical intervention to better suit end users and should also provide a platform for future research. The interviews will aim to capture participants’ experiences and perceptions of the intervention, providing valuable insights about any impact on their daily lives. Similarly, for the carers, we hope to explore their perception of how the intervention affects their care recipient’s coping ability and whether the caregiver notices any change in the burden of care.

The semistructured interview transcript can be found in Multimedia Appendix 1.

### Inclusion and Exclusion Criteria

The proposed participant eligibility criteria are shown in Textbox 1.

Participant eligibility criteria.
**Inclusion criteria**
Clinical and spirometric diagnosis of moderate to severe chronic obstructive pulmonary disease (COPD) with forced expiratory volume in 1 second (FEV1) <80% predicted and FEV1/forced vital capacity ratio <70%Severe breathlessness with modified Medical Research Council score ≥2Aged ≥40 years
**Exclusion criteria**
Bed-bound or moribundCognitive impairment that precludes ability to engage and participate in education strategiesCurrent active diagnosis of cancer, substance abuse (other than nicotine dependence), or other uncontrolled medical or psychiatric disorderModerate or severe exacerbation of COPD (defined as an escalation of treatment to include systemic corticosteroids and/or antibiotics [10]) within 4 weeksInsufficient command of the English language to comprehend and engage with interventionsCurrent enrollment in pulmonary rehabilitation program (may participate if still eligible upon program completion or if involved in a long-term maintenance program)

Description of Intervention: MBC

The proposed intervention, the MBC, is a 9-week program to manage chronic refractory breathlessness. The MBC team will include a respiratory physician, occupational therapist, specialist respiratory nurse, and physiotherapist with referrals as needed for dietetic and speech pathology services. The MBC itself will comprise 9 health care interactions of 60 to 90 minutes, with most visits occurring within the patient’s home as outlined in Table 1.

**Table 1 table1:** Macarthur Breathless Clinic 9-week program.

Schedule	Location	Activity
Week 1	Patient’s home	Initial assessment, respiratory nurse
Week 2	Outpatient clinic	Medical assessment by respiratory physician Multidisciplinary team assessment of breathlessness, contributing factors and impacts to develop recommendations and management plan Introduction to nonpharmacologic strategies, including provision and use of a battery-operated handheld fan Fact sheets on managing breathlessness
Week 3	Patient’s home	Physiotherapist
Week 4	Patient’s home	Occupational therapist
Week 5	Patient’s home	Respiratory nurse
Week 6	Patient’s home	Physiotherapist
Week 7	Patient’s home	Respiratory nurse
Week 8	Patient’s home	Final assessments, research assistant
Week 9	Outpatient clinic	Closure and follow-up arrangements, multidisciplinary team

An initial holistic medical assessment will be performed by an experienced multidisciplinary team, including a respiratory physician, specialist respiratory nurse, and respiratory physiotherapist. The holistic assessment framework that will be used for breathlessness is systematic and encompasses the skill set of the multidisciplinary team ensuring the whole person is considered. The assessment template in Multimedia Appendix 2 outlines the domains considered. The assessment recognizes the multifactorial nature of breathlessness, with possible contributions from many interconnected parts, including medical history, comorbid diseases, medications, mental and social factors, understanding and beliefs about breathlessness, self-management strategies, inhaler technique, current functional capacity, exercise history, and even incontinence.

Following initial assessment and optimization of medications, nonpharmacological therapies will commence. Through the MBC, patients and carers will receive education about breathlessness management and daily coping strategies to enhance independence and productivity. The clinical team will coach participants through individualized strategies to improve management of breathlessness in daily activities (Table 2) based on Cambridge Breathlessness Intervention Service’s “breathing, thinking, functioning” clinical model [11]. A broad repertoire of standard interventions will be tailored to individual patients’ needs, goals, and preferences.

**Table 2 table2:** Nonpharmacologic breathlessness interventions.

Theme	Examples
Beliefs	Validation of breathlessness Clarifying mistaken beliefs—for example, breathlessness is not always due to low oxygen levels and breathlessness itself is not dangerous Motivational interviewing
Strategies	Use of a handheld battery-operated fan Breathing techniques such as “breathing around a rectangle,” “pursed lip breathing,” “flickering the candle,” “paced breathing,” or “diaphragmatic breathing” explained with an accompanying fact sheet Positions to relieve breathlessness Sputum clearance techniques
Exercise	Walking program with use of a pedometer Strengthening exercises
Aids/efficiency	Shower chair 4-wheel walker Energy conservation Home modifications Referral to dietitian if underweight or malnourished
Education and self-management	Inhaler technique Disease education (including medications and other therapies) Written breathlessness action plans Written chronic obstructive pulmonary disease exacerbation action plan Breathlessness DVD to reinforce key interventions Relaxation CD Fact sheets on managing breathlessness
Miscellaneous	Carer support Assessment and management of incontinence

The role of each clinician and coaching topics covered is illustrated in Figure 2, noting that any cross-over of topics between clinicians will serve as reinforcement of strategies provided or will allow colleague cross-cover.

**Figure 2 figure2:**
[figure not shown]
Clinician roles and coaching topics. COPD: chronic obstructive pulmonary disease; MDT: multidisciplinary team.

There will be fortnightly multidisciplinary team case conferencing of all participants during their 9-week intervention. Case conference discussion will aim to review and/or revise patient goals and optimize, coordinate, troubleshoot, and plan intervention activities. At the patient’s final outpatient clinic review, the multidisciplinary team will revisit patient goals, discuss next steps, and seek informal feedback on the program.

### Outcome Measures

#### Breathlessness Outcomes

The proposed primary outcome is mastery of breathlessness, as measured by the Chronic Respiratory Questionnaire (CRQ) subscale of mastery [12].

The proposed secondary outcomes, described below, will measure the impact of the intervention using several scales to provide a full understanding of change across a number of dimensions.

The CRQ is a validated measure of quality of life used in chronic lung diseases, with a particular emphasis on breathlessness. It consists of 4 subscales: dyspnoea, fatigue, emotion, and mastery. In each scale, higher scores reflect better health. The minimal clinically important difference (MCID) for each subscale individually is an increase of 0.5 on a 7-point scale, with a change of 1 representing a moderate change and 1.5 a large change [12].

For breathlessness intensity, unpleasantness, and confidence numerical rating scales, international guidelines recommend assessing both intensity and unpleasantness of breathlessness [13]. The MCID for these measures is a change of 1 unit [14].

The COPD Assessment Test (CAT) is a validated 8 item tool that provides a reliable measure of the impact of COPD on a patient’s health status. Higher scores reflect worse health with an MCID of 2 [15].

The Hospital Anxiety Depression Scale is a 14 item self-reported measure with anxiety and depression subscales each with 7 items. An MCID of 1.5 points for Hospital Anxiety Depression Scale in COPD populations has been suggested [16].

The EQ-5D-5L is a standardized measure of health status that provides a simple, generic measure of health for clinical and economic appraisal. The scale explores the degree of difficulty across 5 domains: mobility, self-care, usual activities, pain or discomfort, and anxiety or depression. A weighted index value will be derived, ranging between −0.59 and 1, which can be converted to quality-adjusted life years based on the Australian values set. Higher scores reflect better health, and the mean MCID is 0.051. It also includes a visual analog scale 0 to 100, rating overall health from worst to best with a mean minimum important difference of 6.9 (range 6.5-8.0) [17].

Pedometer readings of average number of steps per day over the past 7 days will be recorded. There is no consensus regarding the MCID for this measure.

The Dalhousie Dyspnoea and Perceived Exertion Scale tracks dyspnea and perceived exertion. The scale consists of 7 pictures representing breathing effort, chest tightness, throat closure, and leg effort, with increasing severity depicted in the pictures, traversing from left to right [18].

#### Health Care Resource Use Outcomes

Self-reported exacerbation, emergency department (ED) visit, and hospitalization data will be collected. South Western Sydney Local Health District’s electronic medical records will also be systematically reviewed to verify participant self-reports. Data will be updated at 6 and 12 months from MBC enrollment and will include the annual number of the following:

ED presentations (all presentations), lasting <24 hours, that do not result in hospitalization, as well as breathlessness-related ED presentations, lasting <24 hours, that do not result in hospitalizationUnplanned hospitalizations, including unplanned hospitalizations due to breathlessnessHospital length of stay in bed days (all unplanned hospitalizations), as well as breathlessness-related hospital bed daysExacerbations of COPD counted by patient-reported activation of COPD action plan, along with occasions of prescription of antibiotics and/or corticosteroid for the treatment of symptoms of respiratory exacerbation during hospitalized events

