#### Statistical Analysis Plan

Descriptive statistics will be applied to the study population to characterize them in terms of demographic and baseline clinical parameters. Normally distributed continuous variables will be expressed as mean (SD), nonparametric variables will be defined by median and range, while categorical variables will be expressed as percentages.

Breathlessness outcomes will be compared across 3 time points: baseline, 9 weeks, and 52 weeks using repeated measures ANOVA. Predictors of response will be sought using linear regression models with sex, forced expiratory volume (FEV) in 1 second, ratio of FEV to forced vital capacity, BMI, Montreal Cognitive Assessment, and baseline anxiety and depression scores as prespecified variables. Health care use measures and exacerbation data for the 12 months prior to MBC enrollment will be compared with the corresponding values for the 12 months after MBC enrollment, using Student 2-tailed *t* tests or nonparametric tests as appropriate. Protocol completer and dropout populations will be compared in terms of baseline characteristics (sex, age, FEV in 1 second, pack years, BMI, CRQ-Mastery subscale, CAT score, and Montreal Cognitive Assessment) to investigate potential selection bias.

Finally, comparison will be made with patients’ baseline data from the year prior to enrollment in the breathless clinic, benchmarked against nonparticipant comparator hospital deidentified patient medical records with (1) ED presentations for reasons of breathlessness, triaged as “shortness of breath—respiratory” or (2) hospitalized with exacerbations of COPD or heart failure as per diagnostic related group assignment. These benchmarking comparisons will use deidentified electronic medical records and will contribute to exploratory analyses undertaken to better understand the health care use of our sample cohort in the context of the overall health care use patterns of our local population “breathless” groups.

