However, this study has several limitations that must be acknowledged. First and foremost is the nonrandomized study design; all recruited participants will receive the intervention and act as their own controls. This design could introduce both time and attrition bias and is a clear limitation on the level of evidence produced. The authors were aware of a randomized controlled trial [8] underway in another Australian center using a similar model to our protocol, and we therefore chose a nonrandomized study design to address clinical need while still demonstrating translatability to a different population and setting. Given that COPD is a chronic and progressive disease, evaluating the impact of breathlessness over time may still yield valuable insights, provided the results are interpreted carefully. While potential mortality among participants with more severe disease may skew study results, on the other hand, worsening disease trajectory may mask benefits when determining results over the longer term. Considering this, even if patients appear to be stable with respect to outcome measures at 12 months, this may actually represent improvement compared with the expected trajectory in COPD, which is one of deterioration. In fact, clinically significant breathlessness is a known marker of poor prognosis for patients with COPD [21], and so our target population will be expected to deteriorate more rapidly than the COPD group as a whole.

The study’s proposed setting, a single metropolitan center situated within a large semirural area, may limit the general applicability of our results. However, the authors are aware of concurrent research on this topic being conducted at other centers and health districts throughout Australia, which should help to address this.

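### Annual health care use is compared before and after enrollment by tests that carry no exposure time, although the second year can be cut short by death or loss

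*Protocol article*

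**What the plan says.** Under Health Care Resource Use Outcomes the measures are defined as yearly totals: "Data will be updated at 6 and 12 months from MBC enrollment and will include the annual number of the following", followed by ED presentations, unplanned hospitalizations, bed days and exacerbations. The district's electronic records are also searched, with the stated purpose of verifying what participants report.

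Under Statistical Analysis Plan the prior-year values are compared with "the corresponding values for the 12 months after MBC enrollment, using Student 2-tailed" t tests or a nonparametric alternative; the full test wording is "using Student 2-tailed *t* tests or nonparametric tests as appropriate". Study Design adds: "Quantitative outcomes will be evaluated with participants acting as their own controls, before and after the clinic intervention".

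The article expects follow-up to be incomplete. Sample Size states: "we have set our recruitment goal at 92 participants, in anticipation of 30% (n=31) discontinuation or dropout". Strengths and Limitations says: "While potential mortality among participants with more severe disease may skew study results". That section also names attrition bias in general terms. The only planned analysis of loss compares completers and dropouts on baseline variables, and prior-year health care use is not among those listed.

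**The concern.** The two periods are not alike. To be enrolled, a person must have survived the prior year, so the before count always covers 12 months. The after count covers 12 months only for those who neither die nor are lost to observation. A t test or a rank test on annual numbers treats both as full years.

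Reduced COPD-related health care use is the second hypothesis in the Introduction. If shortened years enter as they stand, lost time appears as reduced use, in the direction hoped for. If those participants are left out instead, the result may describe people at lower risk than the enrolled cohort.

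**Working it through.** **The plan's own figure.** 0.30 × 92 = 27.6, so 28 participants, not 31. 31/92 = 33.7%, and 31/0.30 = 103. The figures 92, 30% and 31 do not agree with one another. I use 30% and show 33.7% as a variant.

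**Inputs.** From the article: 92 participants, 30% loss, 12 months before against 12 months after, within-person control. Assumed, because the article gives no value: when loss occurs, the event rate, how loss relates to risk, and a two-sided 5% test. No true effect is assumed throughout.

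**A. Partial years entered as raw counts, loss unrelated to risk.** With share lost f and mean fraction of the year observed among those lost m, the spurious fall is f × (1 − m).

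| f | m | Spurious fall |
|---|---|---|
| 0.30 | 0.50 (even loss) | 0.30 × 0.50 = 15% |
| 0.30 | 0.75 | 0.30 × 0.25 = 7.5% |
| 0.30 | 0.25 | 0.30 × 0.75 = 22.5% |
| 0.337 | 0.50 | 0.337 × 0.50 = 17% |
| 0.20 | 0.50 | 0.20 × 0.50 = 10% |
| 0.10 | 0.50 | 0.10 × 0.50 = 5% |

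A simulation of a paired t test (92 participants, Poisson counts with gamma frailty of shape 1, even loss, 20,000 replicates) falsely declared a reduction in 17%, 28% and 36% of trials at 1, 2 and 3 events per year with 30% lost. With 10% lost it was 5% to 8%. The nominal figure in that direction is 2.5%.

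**B. Participants with short years dropped.** If each person's rate is constant, a stayer has the same expected count in both years, so the paired ratio is 1.00. What changes is who is described. As an illustration, let individual rates follow a gamma distribution with shape 1 and mean 1, and let the exit hazard be h times the individual rate.
- Exit share is 1 − 1/(1 + h). For 30%, h = 0.30/0.70 = 0.429.
- Stayers' mean prior-year rate, relative to everyone's, is 1/(1 + h) = 0.70.
- An unpaired comparison of stayers' second year with everyone's first year would therefore show a false 30% fall. In this model raw partial counts fall by the same 30%.

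**C. Which person-time model works.** In the same model mean person-time is ln(1 + h)/h = 0.357/0.429 = 0.832 year.
- Pooled events per person-year: 0.70/0.832 = 0.84, still a false 16% fall. With h = 0.5 (33% exit) the ratio is 0.667/0.811 = 0.82, an 18% fall. An offset with participant only as a cluster does not cure risk-related loss.
- Conditioning on the participant: with rate λ and observed second-year time t, the expected second-year count is λt and the expected total is λ(1 + t). At a rate ratio of 1 the second year's expected share of the total is t/(1 + t), and λt − λ(1 + t) × t/(1 + t) = 0 for every participant, whatever λ is. The estimate is therefore centred on no effect.

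**D. Days alive and out of hospital.** Nobody can die in the prior year. If 10% die evenly over the second year, 0.10 × 0.5 × 365 ≈ 18 days per participant are lost with no effect on hospital use. That biases the before-after contrast the other way.

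**The case against.** A reader might infer that attrition will show up as reduced use in this trial, or that death will count as a good outcome. The documents do not support so firm a statement, for four reasons.

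- The analysis set is not stated. The own-control design and the separation of completers from dropouts are both compatible with a paired completers' analysis, which gives about 0% spurious fall under constant rates.
- Discontinuation or dropout need not end observation, because district records can still be searched after someone stops answering questionnaires. Only death necessarily ends exposure to hospital events, and no mortality figure is given.
- The Results section reports 92 participants finishing, equal to the whole recruitment goal, so actual attrition is unclear.
- The 30% falls under risk-related loss rest on an assumed frailty model.

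Nonparametric tests are also allowed, which largely answers any complaint about skewed counts. It does not answer the exposure problem, which rank tests share.

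It can also be said that handling of death and loss belongs in a full analysis plan, and that the article admits attrition bias. That stands for detail the article leaves out. But the article does state the outcome form (yearly totals), the contrast and the tests, and as stated these have no place for exposure time. Records are described as a check on self-report, not as a means of completing follow-up. The completer-dropout comparison may reveal selection; it does not correct the comparison.

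**Conclusion.** The point holds as a weakness of the stated method for a secondary outcome. If partial years are used as raw counts, the bias favours the second hypothesis: about 15% at 30% loss spread evenly over the year, 7.5% to 22.5% according to timing, and about 5% at 10% loss. If such participants are dropped and the comparison is paired, there is no such bias under constant individual rates, but the result may apply to a lower-risk group than was enrolled. Which of these will happen, and how much follow-up was actually lost, cannot be told from the article. The sizes assume no true effect and, for the 15% and its range, loss unrelated to risk.

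**What to change.** 1. Use the district records, already reviewed for verification, to capture ED visits, unplanned admissions and bed days for all enrolled participants to 12 months or death, within consent and regardless of questionnaire dropout.
2. Compare the periods within participant with a count model that conditions on the participant (for example conditional or fixed-effect Poisson with robust variance) and has log person-days at risk as offset. Do not rely on a pooled offset with clustering alone. Report rate ratios with 95% CIs.
3. Give a completers-only paired analysis as sensitivity, and state how many participants lack a full 12 months and why.
4. Report deaths alongside. Do not make before-after days alive and out of hospital the main contrast, because survival through the prior year is guaranteed.

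The cost is analysis wording and some extra record review; the article says analysis is still under way. Out-of-district and self-treated events will be missed after withdrawal, so person-time for self-treated exacerbations should end at last contact. The conditional model assumes that a participant's rate is otherwise stable and that an event does not itself bring follow-up to an end. Where admissions precede death, some bias can remain, which is another reason to show deaths beside the rate ratios.
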